**Methods/Design:**

Sixty women, aged 18–50 years with a body mass index (BMI) greater than 34.9 kg.m^2^ and at least one obesity-related co-morbidity, will be recruited for this 12-month study. Participants will be randomised to either exercise plus energy restriction (*n* = 30), or energy restriction alone (*n* = 30). All participants will follow an energy-restricted individualised diet incorporating a VLED component. The exercise intervention group will also receive exercise by supervised aerobic and resistance training and a home-based exercise programme totalling 300 minutes per week. Primary outcome measures include body composition and aerobic fitness. Secondary outcome measures include: physical function, cardiometabolic risk factors, quality of life, physical activity, and mental health. All outcome measures will be conducted at baseline, 3, 6 and 12 months.

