### Sample size

The number (*n* = 60) of participants to be recruited for this study has been determined based on previous evidence, plus a projected drop-out rate of 25 %, and provide adequate statistical power for the two co-primary outcome measures of VO_2peak_ (*n* = 20, *α* = 0.05, power 0.9 [74]) and lean mass (*n* = 23, SD of 1.7, *α* = 0.05, power 0.8 [75]). Secondary outcome measures for traditional markers of cardiometabolic health including systolic and diastolic blood pressure, total cholesterol, LDL cholesterol, insulin sensitivity; and measures of physical activity require fewer participants to reach statistical power (range *n* = 8–14, *α* = 0.05, power 0.8).

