### Statistical analysis

All variables will be plotted and visually inspected for skewness and kurtosis. Formal analysis of normality will be confirmed with the Kolmogorov-Smirnov test of normality (SPSS statistics for windows, version 21.0: IBM Corp., Armonk, NY, USA) as it is appropriate when used with small- to medium-sized samples [110]. The independent *t* test for continuous variables will be used to examine the groups (ER versus EXER) characteristics at baseline using Genstat statistical software (for Windows 16th edition. VSN International, Hemel Hempstead, UK). Genstat will be used to produce a histogram of residuals, fitted-value and normal plot of residuals and assessed for normality, independence, equal variance and linearity for each dependent variable. If the data is shown to not be normally distributed or displays heteroscedasticity the data will be log transformed to restore normality [111]. Factorial repeated measures analysis of variance (ANOVA) (mixed between-within subjects or split-plot) with intention-to-treat protocol for all variables to assess the interaction effect (group × time) will be performed. Missing values for variables will be replaced using an expectation maximisation algorithm with a multiple imputations method [112] using Genstat statistical software. Analysis for the least significant difference of the means will be performed for both time and group with a *p* value set at 0.05.

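### The group × time test is followed by uncorrected LSD on time and on group, and under either literal reading that step gives no sound between-arm comparison for the co-primary outcomes

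*Protocol article*

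**What the plan says.** In the protocol article, the Statistical analysis section sets the main model: "Factorial repeated measures analysis of variance (ANOVA) (mixed between-within subjects or split-plot) with intention-to-treat protocol for all variables to assess the interaction effect" of group by time. Two arms and four visits (baseline and months 3, 6 and 12, from the Measures section) give that interaction 3 degrees of freedom. The next step is "Analysis for the least significant difference of the means will be performed for both time and group", at 0.05. The section names no multiplicity adjustment for this step and does not condition it on the interaction.

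The Sample size section says that the numbers "provide adequate statistical power for the two co-primary outcome measures", peak VO2 and lean mass. For lean mass it gives "lean mass (*n* = 23, SD of 1.7, *α* = 0.05, power 0.8 [75"], and for peak VO2 only n = 20, α = 0.05 and power 0.9. It states no effect size, visit, sidedness or test. Baseline measures are completed before allocation (Randomisation section), and both arms follow the same dietary protocol (Energy restriction section).

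**The concern.** The trial asks whether exercise added to the diet gives better outcomes than the diet alone. That is a difference between arms in change from baseline.

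A comparison of visits averaged over arms mainly shows what the shared diet does. A comparison of arms averaged over all visits includes one visit at which no effect can exist, and it retains the full between-woman variation. If LSD instead compares the arms visit by visit, there are three chances per outcome to declare a difference at an unadjusted 0.05.

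The interaction F is aimed at the right question, but a significant result does not say when, or in which direction, the arms differ. With about 23 completers per arm, the choice of comparison could decide the conclusion.

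**Working it through.** **Inputs from the protocol article.** Total 60, 30 per arm; drop-out 25 %; lean mass n = 23, SD 1.7, α 0.05, power 0.8; four visits including baseline.

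**Assumptions.** n = 23 is per arm. The lean-mass comparison is two-sided between two groups. SD 1.7 is the SD of change, in kg. Correlation between visits is equal. The between-woman SD of lean mass, S, is 4 to 8 kg (not given in the article).

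**1. The plan's own total.** 23/(1 − 0.25) = 30.7, so 31 per arm and 62 in all. Alternatively 23 × 1.25 = 28.75, so 29 per arm and 58 in all. Both are within 2 of the stated 60, which supports reading 23 as per arm; 23 in total would inflate only to 31.

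**2. Implied lean-mass difference.** δ = 1.7 × (1.960 + 0.842) × √(2/23) = 1.40 kg by the normal formula, or 1.44 kg with the t distribution.

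**3. Reading A: LSD on marginal means.** An effect δ at all three follow-ups and none at baseline averages to (0 + δ + δ + δ)/4 = 0.75δ = 1.08 kg. The implied correlation is ρ = 1 − 1.7²/(2S²), the SD of a woman's four-visit mean is S√((1 + 3ρ)/4), and the standard error of the arm difference is that SD × √(2/23).

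| S (kg) | ρ | SD of mean | SE | Power for 1.08 kg |
|---|---|---|---|---|
| 4 | 0.910 | 3.86 | 1.14 | 15 % |
| 6 | 0.960 | 5.91 | 1.74 | 9 % |
| 8 | 0.977 | 7.93 | 2.34 | 7 % |

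**4. Reading B: arms compared at each of three follow-ups.** Simulation under no effect, 23 per arm, 20,000 runs, each comparison at 0.05; rate of at least one significant result per outcome:

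| ρ | On levels | On change from baseline | Change, only after a significant interaction |
|---|---|---|---|
| 0.5 | 12.6 % | 12.8 % | 4.2 % |
| 0.8 | 9.6 % | 12.4 % | 3.8 % |
| 0.95 | 7.4 % | 12.9 % | 3.9 % |

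**5. Power of the interaction test.** The noncentrality is λ = (n/2) Σ(d_t − d̄)² / (1.7²/2), where d_t is the arm difference in change at visit t, n = 23 and the peak difference is 1.44 kg.
- Full effect at all follow-ups, or at one only: λ = 12.3, power 0.84.
- Growing (0.25, 0.5, 1) or fading (1, 0.5, 0.25) effect: λ = 9.0, power 0.70.
- Full at 3 months, then half: λ = 8.2, power 0.65.

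A single contrast at the visit with the full effect has power 0.80 by construction.

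**6. Gain from baseline adjustment.** The variance relative to a change score is (1 + ρ)/2, a saving of (1 − ρ)/2. With the ρ values in step 3 this is 4.5 %, 2.0 % and 1.1 % for S = 4, 6 and 8 kg. At ρ = 0.5, possible for other outcomes, it would be 25 %.

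**The case against.** Several counter-arguments stand.

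- **Sizing.** A reader might infer that the interaction is not the comparison the trial was sized for. The document does not support that. A lone SD with α and power suggests a simple two-group comparison, but the Sample size section never states one. What can be shown is that the two sections cannot be linked.
- **Baseline.** A reader might infer that baseline is ignored. It is not: it is a level of time, so the interaction tests differential change. Omitting it as a covariate costs precision, not validity, and for lean mass the cost is small (step 6).
- **Weakness of the omnibus test.** It is not uniformly weaker than a single contrast; with a constant effect it does slightly better (0.84 against 0.80).
- **The two LSD readings exclude each other.** Dilution and three-visit inflation cannot both apply. The low power in step 3 also belongs to a comparison that the plan does not call its treatment test.
- **Protected LSD.** If LSD were used only after a significant interaction, the error rate would be about 4 % per outcome. The ANOVA is described first, which makes this possible, but the text does not say it.
- **A separate analysis plan** may name the contrast, visit, covariates and any sphericity correction. Their absence from an article is not the point here. The LSD sentence is published as the rule, and a later plan would have to override it.

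**Conclusion.** The point holds in limited form. As written, LSD at 0.05 on time and on group does not give a sound treatment-effect conclusion under either literal reading. Read as marginal means, it addresses the wrong quantity: a constant effect is cut to 3/4, with about 7 to 15 % power for a 1.44 kg lean-mass effect if S is 4 to 8 kg. Read as visit-by-visit arm comparisons, it carries about a 7 to 13 % chance of a false positive per outcome, depending on the correlation and on whether levels or changes are compared. Conditioning on the interaction would remove that inflation, but the article does not state such a condition.

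The interaction test is valid for differential change but supplies no single effect estimate, and its power ranges from 0.65 to 0.84 with the time course. The 3/4 dilution is pure arithmetic. The power figures rest on the assumptions listed in the working, in particular that 1.7 is an SD of change and that 1.44 kg, back-solved from the sample size, is the difference of interest.

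**What to change.** 1. Delete LSD on the time and group main effects.
2. For each co-primary, pre-name one follow-up visit; the article names none, so the amendment must choose it. Make the primary test the EXER minus ER difference at that visit, adjusted for the baseline value, from a repeated-measures mixed model, with its 95 % CI.
3. Report the other follow-up visits as secondary with Holm adjustment, and keep the group × time interaction as supportive.
4. State in the Sample size section which comparison, visit and difference the lean-mass and peak VO2 numbers refer to, so that it matches the primary test.

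No new data are needed. The cost is a few degrees of freedom for the model and a commitment to one visit, which loses power if the effect peaks at another. The existing imputation sentence must be made consistent with the mixed model. This change does not settle how the two co-primaries combine into one conclusion; that needs its own statement.

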### Randomisation

Participants will be randomised individually by a researcher external to the project and will have no contact with the participants prior to or during the trial. This researcher will have no intellectual or personal investment into the study design or outcomes. The women will be randomised into either (ER) or (EXER) groups using sealed opaque envelopes in blocks of six. The envelopes will be stored in a locked cabinet within the independent researcher’s office. Each envelope will contain a single sheet of paper identifying the group allocation. The sheet of paper will be folded at least twice to reduce chance of transparency. One envelope will be chosen at random from the stack of six envelopes containing three of each group allocation (EX and EXER) reduced to a single envelope; this is then combined with the next group of six envelopes to reduce the chance of predictability. The independent researcher is provided with a participant identification number and completes randomisation once the prospective participant provides the study investigators ([name]) with a medical clearance from their own general practitioner, preliminary participant screening, and completes all of the baseline measures to ensure safety and suitability for study participation. Participants, and researchers involved in delivering participant interventions will not be blinded to group allocation. Some of these researchers ([name]) will also be involved in study co-ordination and data collection.

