#### Exercise training

EXER follow a standardised progressive exercise programme led by accredited exercise physiologists or a student exercise physiologist supervised by an accredited exercise physiologist. The exercise intervention consists of a supervised exercise programme that is complemented by a home-based exercise routine. The supervised exercise training will commence the same week as the VLED and consists of the following:3 × 1 hour supervised exercise sessions per week (weeks 1–6)2 × 1 hour supervised exercise session per week (weeks 7–12)1 × 1 hour supervised exercise session per week (weeks 13–26)2 × 1 hour supervised exercise sessions per month (weeks 27–52)

The exercise training will consist of a progressive moderate intensity aerobic conditioning and resistance training programme using a variety of machines and free weights. Each training session lasts 60 minutes and will consist of 5 minutes’ warm up, 45–50 minutes of conditioning, and 5 minutes of cool-down and stretching. The conditioning component consists of approximately 20–30 minutes of aerobic training (12–16 on Borg’s Ratings of Perceived Exertion (RPE) scale, 60–80 % heart rate reserve (HRR)) followed by 20–30 minutes of resistance exercise (one to three sets of eight to ten repetitions). The resistance exercise involves six to ten different, predominantly multi-joint exercises for the upper and lower extremities at an intensity of two repetitions below volitional fatigue, with a 2-second concentric and eccentric contraction speed. Exercise prescription followed clinical judgement and the American College of Sports Medicine’s (ACSM’s) guidelines [76] to ensure fitness improvement and programme compliance. Once participants complete three sets of ten repetitions with correct technique, for two consecutive training sessions, the resistance will be increased. The cardiorespiratory fitness training progress from 40–60 % HRR in the first 5 weeks to 60–80 % HRR for the remainder of the programme. The mode of aerobic exercise varies depending on participant’s choice; however, weight-bearing exercise such as walking will be encouraged as one of the principle exercise modes.

The exercise physiologists will follow a structured resistance training programme with eight core exercises that will include: leg press, squats, bench press, seated row, lateral pull down, shoulder press, biceps curl and triceps kickbacks.

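### The follow-up comparisons are unadjusted LSDs with no stated gate, no defined set of means and no deciding visit, so the per-outcome error rate and the treatment effect are left open

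*Protocol article*

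**What the plan says.** All of the following is in the protocol article.

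- **Statistical analysis.** A factorial repeated measures (split-plot) ANOVA "for all variables to assess the interaction effect (group × time) will be performed". Then: "Analysis for the least significant difference of the means will be performed for both time and group with a" p "value set at 0.05". No adjustment for multiple comparisons is stated, and no condition links the second step to the first.
- **Abstract, Methods/Design.** "All outcome measures will be conducted at baseline, 3, 6 and 12 months". That makes four visits, three of them after randomisation. Neither this section nor Measures singles out a visit.
- **Sample size.** The number recruited is meant to "provide adequate statistical power for the two co-primary outcome measures of" VO2peak and lean mass. Each outcome has one n, one alpha and one power, tied to no visit.
- **Randomisation.** Allocation takes place once the participant "completes all of the baseline measures to ensure safety and suitability for study participation", so the baseline visit precedes allocation.
- **Exercise training.** Supervision starts at three one-hour sessions a week and ends, in weeks 27-52, at two "supervised exercise sessions per month". The home programme takes over, and the weekly target of 300 minutes is held from week 6 to month 12.

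**The concern.** The trial asks whether adding exercise to the diet gives better results than the diet alone. With two arms and four visits, the group × time test has (2 − 1) × (4 − 1) = 3 degrees of freedom. A significant result says that the two profiles are not parallel. It does not say at which visit they differ, in whose favour or by how much. The LSD step has to supply all of that, and its one sentence can be read in three ways:

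1. **Visit by visit, always done.** Each of three follow-up visits gets a full 5 % test.
2. **Visit by visit, only after a significant interaction** (protected LSD).
3. **Marginal means**, that is, the group means averaged over all four visits and the time means averaged over both groups.

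These differ in error rate and in what they estimate. With no deciding visit, a benefit could be reported at whichever visit crosses 0.05, although the sample size was planned as one test per outcome.

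**Working it through.** **Inputs.** From the article: four visits, alpha 0.05 (taken as two-sided), 30 women per arm, and for lean mass n = 23, SD 1.7 and power 0.8. Not given, so assumed: equal correlation r between any two visits (compound symmetry), with r from 0.3 to 0.9.

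**The plan's own figure.** Read n = 23 as per arm, so 46 in total. With a "projected drop-out rate of 25" % allowance, 46 / 0.75 = 61.3, so 62; or 46 × 1.25 = 57.5, so 58. The stated 60 lies between the two. No effect size is given. Back-solving gives 1.7 × (1.96 + 0.84) × √(2/23) ≈ 1.40 by the normal formula, or 1.44 with the t distribution. This is one difference tested once.

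**Reading 1, ungated, three visits.**
- Upper reference, independent tests: 1 − 0.95³ = 14.3 %.
- Single-visit means (simulated): 13.6 % at r = 0.3, 12.5 % at 0.5, 10.9 % at 0.7, 8.4 % at 0.9. The range is about 8-14 %.
- Change from baseline: under compound symmetry each change has variance 2σ²(1 − r), and two changes share covariance σ²(1 − r). Their correlation is therefore 0.5 whatever r is, and the rate stays near the 12.5 % found above for correlation 0.5. Simulating the full ANOVA with 30 per arm gives 12.3-12.6 % for r = 0.5 to 0.9.

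**Reading 2, gated on a significant interaction.**
- No effect at any visit: 3.8-4.4 % for change from baseline, and 0.7-2.9 % for single-visit means. Both are below 5 %.
- True effect at 3 months only, of one SD of change, 30 per arm: the gate opens in over 98 % of trials, and a false difference at 6 or 12 months is declared in about 9 % (8.8-9.2 % across runs). Two independent tests would give 1 − 0.95² = 9.75 %.

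**Reading 3, marginal group means.** The expected group difference at baseline is zero.
- Effect d at all three follow-up visits: (0 + d + d + d) / 4 = 0.75d.
- Effect building in equal steps over the visits: (0 + d/3 + 2d/3 + d) / 4 = 0.50d.

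**The interaction test itself.** Take d = 1.436 at every follow-up visit and 1.7 as the SD of change, so the within-woman error variance is 1.7² / 2 = 1.445. The squared deviations of (0, d, d, d) from their mean sum to 0.75d² = 1.547. The noncentrality is (n/2) × 1.547 / 1.445, which is 12.3 at 23 per arm and 16.1 at 30 per arm. Power is about 84 % and 93 %.

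**Price of control by adjustment.** Bonferroni over three visits uses 0.05 / 3 = 0.0167. At a difference of 1.40 it needs 31 per arm instead of 23 for 80 % power. A single named visit needs no such increase.

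**The case against.** The strongest reply is that the article makes group × time the effect to be assessed. That is one 5 % test per outcome. It is not diluted as the group main effect is, and it has 84-93 % power on the inputs above. If the LSDs only follow a significant interaction, the error with no effect anywhere stays near 4 %. This stands, and it rules out two stronger readings.

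- A reader might infer that the plan must either dilute the effect or carry a 12 % error rate. The documents do not support that. The gated reading is a natural one, and 12 % applies only if there is no gate.
- A reader might infer that lean mass is left with almost no power. That figure would belong to the group main effect, which the plan does not name as its test. It would also need a cross-sectional SD that the article does not give. Even on the article's 1.7, at 23 per arm and a sustained effect, it runs from 76 % (r = 0.5) to 59 % (r = 0.9) if 1.7 is a single-visit SD, or to 16 % (r = 0.9) if it is an SD of change. Nothing firm can be quoted.

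Two further replies stand in part. The 9 % case has a true effect at one visit, so the broad claim that exercise helps would be right and only its timing wrong. Also, although supervision tapers, the target exercise volume does not, so the taper alone does not show that early and late visits ask different questions.

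Finally, a gate, a deciding visit and exact contrasts may be in an analysis plan not shown here. That excuses their absence as such. It does not excuse the sentence that the article does contain, which fixes an unadjusted method for ambiguously described comparisons.

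**Conclusion.** The point holds as a defect in a stated method. The LSD step is unadjusted, its link to the interaction is unstated, the means it compares are undefined, and no visit is named to decide.

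- Ungated: about 12 % per outcome for change from baseline, about 8-14 % for single-visit means.
- Gated: about 4 % with no effect at any visit, but about 9 % for a false claim at the remaining visits once a true effect at one of them opens the gate. Gating helps, but does not control error when the effect is present at some visits only.
- Marginal group means: a sustained effect shrinks to 75 %, so this comparison should not serve as the treatment effect.

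The error rates assume two-sided tests and compound symmetry. The single-visit range depends on a correlation that the article does not give. The 9 % is for an effect of one SD of change at 3 months and none later. The dilution to 75 % needs only randomisation after baseline and an equal effect at every follow-up visit.

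**What to change.** Replace the LSD sentence with one pre-named contrast for each co-primary outcome: the EXER minus ER difference in change from baseline at a single visit, estimated from the same model with a 95 % CI. The sponsor should choose that visit before analysis. Twelve months, the end of the intervention, is one candidate, but nothing in the article makes it the only one. Test the other two follow-up visits only under multiplicity control (a fixed sequence or Holm). Report within-arm changes over time descriptively, and do not present the group mean over all four visits as the treatment effect.

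This changes analysis wording only. It adds no participants or visits, and the article reports that recruitment is still under way. The cost is that an effect confined to a visit other than the chosen one would not count as the primary result.

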## Discussion

Previous research demonstrates various health benefits of including exercise training as part of a healthy lifestyle at all BMI ranges. Although clinical practice guidelines recommend exercise training as part of the first-line treatment for overweight and obesity, there are few studies that demonstrate the effectiveness of exercise in class II and class III obesity. The study aims to determine whether the addition of exercise training to a VLED provides more favourable improvements in body composition, physical function, quality of life, and markers of cardiometabolic risk for women with clinically severe obesity, compared to VLED alone. The results of this study should allow for a greater understanding of the benefits and limitations of exercise training for high risk class II and class III obese women during periods of energy-restricted weight loss. It is expected that this research will guide clinical practice in the primary care setting, so that clinicians can provide more informed evidence-based practice for the management of clinically severe obesity.

